### **6.2 Observation Items**

Observation items will be investigated at enrollment and at follow-up visit by various examinations and interview, etc. All the results will be recorded in the corresponding columns of the eCRF.

#### **6.2.1 Observation Items at Enrollment**

1. Enrollment data

Name of institute, date of enrollment, patient enrollment number, patient's initials, and name of the investigator

2. Basic data

Age, sex, height, weight, date of hospitalization, blood pressure at hospitalization, pulse rate at hospitalization

3. Diagnosis of myocardial infarction (MI) or angina pectoris (select from below)

ST-elevation acute myocardial infarction (MI), Non ST-elevation acute MI, stable angina pectoris, unstable angina pectoris, asymptomatic myocardial ischemia, old myocardial ischemia, coronary stenosis

4. History of cardiac diseases

History of PCI, history of CABG, history of myocardial infarction (MI), history of heart failure, history of stroke, history of atrial fibrillation, history of COPD, history of liver cirrhosis, history of malignant tumor, history of hemorrhagic disease

5. Complications

Complication of heart failure at hospitalization, heart failure (current or past history), carotid artery stenosis, disease of peripheral vessels excluding carotid arteries, aortic aneurism/dissection, diseases of the aorta/peripheral vessels (all), diseases of the aorta/peripheral vessels (postoperative/planned to be treated), dialysis

6. Risk factors

Hypertension, Lipid abnormalities, smoking, diabetes mellitus, family history of coronary diseases

7. Concomitant medication

The presence or absence of anticoagulation therapy

8. Coronary angiographic findings

Number of branches affected; presence/absence of following treatments: treatment of unprotected left main coronary artery stenosis, treatment of chronic total occlusion, treatment of lesions responsible for ST-elevation acute MI, treatment of bifurcation lesion, treatment of 2 branches or more, treatment of 3 branches or more; left ventricular ejection fraction, measurement method for left ventricular ejection fraction, mitral insufficiency, evaluation method for mitral insufficiency.

9. Clinical laboratory tests

WBC, RBC, hemoglobin, hematocrit, Plt, creatinine, blood glucose, HbA1c, total cholesterol, HDL cholesterol, triglyceride

10. Cardiac enzymes

Creatine kinase (CK), creatine kinase-MB isoenzyme (CK-MB), troponin T, troponin I

11. Echocardiography (ECG)

Notes: Definition of observation items

1. Diabetes mellitus

Diabetes mellitus is defined as meeting either of 2 hour OGTT glucose level of  $\geq 200$  mg/dL, casual blood glucose level of  $\geq 200$  mg/dL, fasting blood glucose level of  $\geq 126$  mg/dL, or HbA1c  $\geq 6.1\%$  (JDS) or  $\geq 6.5\%$  (NGSP).

When the above tests have not been performed, patients who have been clinically diagnosed as diabetic or are treated with antidiabetic agents are defined as having diabetes.

2. Dyslipidaemia

Patients with total cholesterol  $\geq 240$  mg/dL or HDL cholesterol  $< 40$  mg/dL, or patients who are treated with statins.

3. Evaluation of renal functions

The glomerular filtration rate (eGFR) is calculated by using the equation fitted for Japanese people by the Japanese Society of Nephrology.

$eGFR = 194 * Cr^{-1.094} * Age^{-0.287}$  (\*0.739 for females)  
Terminal renal failure:  $e-GFR < 30 \text{ mL/min/1.73 mm}^2$   
Chronic kidney disease:  $e-GFR < 60 \text{ mL/min/1.73 mm}^2$

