### 4.3 Required examinations

The following examinations are mandatory. Other examinations may be added according to each institute's standards.

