#### At Enrollment:

- Blood tests
  - In this study, hemoglobin and hematocrit concentrations should be measured, because TIMI definition is used to rate hemorrhagic adverse events.
  - Hemoglobin and hematocrit concentrations should be measured also when a hemorrhagic adverse event is suspected during the follow-up period.
  - WBC, RBC, hemoglobin, hematocrit, Plt, creatinine, blood glucose, HbA1c, total cholesterol, HDL cholesterol, LDL cholesterol, triglyceride

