## **9. SUBGROUP ANALYSES**

In this study, patients with different backgrounds are expected to receive the treatment. For this reason, subgroup analyses for diabetes, multiple branch lesions, etc. will be performed, as well as the analysis including all the patients.

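### As worded, the diabetes definition classes enrolled patients with known, treated diabetes as non-diabetic when their mandatory glucose and HbA1c values fall below every threshold

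*Protocol*

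**What the plan says.** The notes to Protocol Section 6.2.1 open the diabetes definition with laboratory criteria: "Diabetes mellitus is defined as meeting either of 2 hour OGTT glucose level of" 200 mg/dL or more, casual glucose of 200 mg/dL or more, fasting glucose of 126 mg/dL or more, or HbA1c of at least 6.1% (JDS) or 6.5% (NGSP). Any one is enough. Diagnosis and treatment come in only through a conditional second sentence: "When the above tests have not been performed, patients who have been clinically diagnosed as diabetic or are treated with antidiabetic agents" are then taken to have diabetes.

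Section 4.3 introduces its list with "The following examinations are mandatory", and the blood tests at enrollment are "WBC, RBC, hemoglobin, hematocrit, Plt, creatinine, blood glucose, HbA1c, total cholesterol, HDL cholesterol, LDL cholesterol, triglyceride". Section 6.2.1 lists blood glucose and HbA1c again among the laboratory items to be recorded.

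The variable is used in Section 9, where "subgroup analyses for diabetes, multiple branch lesions, etc. will be performed". Section 9.1 names Diabetes and Insulin-treated diabetes as the first two of 15 patient-level subgroups. Section 8.1 adds a complementary Cox model to allow for background differences from the RESET XIENCE group, without naming covariates.

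**The concern.** A fallback that applies only to untested patients does nothing in a study that tests every enrolled patient. Antidiabetic treatment aims to bring glucose and HbA1c down, so the patients in whom it succeeds are the ones the laboratory criteria miss. Read literally, the Diabetes subgroup holds only patients above a threshold at enrollment, and the comparison group holds true non-diabetics together with controlled diabetics.

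At stake is the meaning of one pre-specified subgroup, its consistency with a second that is defined by treatment, and possibly one covariate of a complementary model.

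**Working it through.** **Reading the rules together**

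1. Section 6.2.1, first sentence: diabetic if any laboratory threshold is met.
2. Section 6.2.1, second sentence: diabetic by diagnosis or treatment, but only if the tests were not performed.
3. Section 4.3: glucose and HbA1c are performed in every enrolled patient.
4. From 2 and 3, in a patient enrolled per protocol only step 1 operates.

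Take a patient on antidiabetic drugs with HbA1c 6.2% (NGSP) and casual glucose 130 mg/dL. The tests were done, no threshold is met, and the patient is recorded as non-diabetic. If the drug is insulin, the patient belongs by treatment in the Insulin-treated diabetes subgroup but is not diabetic under Section 6.2.1.

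The dyslipidaemia definition in the same notes is built differently: statin treatment is joined to the lipid thresholds by a plain or, so treated patients count whatever their values.

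**Illustrative size**

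The protocol has no figure to reproduce here. Only the sample size N = 1,500 (Section 8.1) comes from the document. Assumed: true prevalence P = 35–45%, share of diabetics below every threshold q = 20–40%, 12-month rates of 6.0% (all diabetics) and 3.5% (non-diabetics).

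- Moved patients M = N × P × q
- Contamination of the recorded non-diabetic group c = M / (N × (1 − P) + M)

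| | P = 35%, q = 20% | P = 45%, q = 40% |
|---|---|---|
| True diabetics | 525 | 675 |
| M | 525 × 0.2 = 105 | 675 × 0.4 = 270 |
| c | 105 / (975 + 105) = 9.7% | 270 / (825 + 270) = 24.7% |

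Section 5 stops enrollment at 1,200. At that size the counts scale by 0.8, to 84 and 216, and the percentages do not change.

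**Effect on the contrast** (true difference 6.0 − 3.5 = 2.5 points)

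*Case A: controlled patients have the same 6.0% rate as other diabetics.* The observed difference is 2.5 × (1 − c):
- 2.5 × (1 − 0.097) = 2.26 points
- 2.5 × (1 − 0.247) = 1.88 points

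*Case B: controlled patients have a different rate r, with all diabetics still averaging 6.0%.*
- Recorded diabetics: (6.0 − q × r) / (1 − q)
- Recorded non-diabetics: 3.5 + c × (r − 3.5)

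With r = 4.0%, q = 40% and c = 24.7%, recorded diabetics have (6.0 − 1.6) / 0.6 = 7.33% and recorded non-diabetics 3.5 + 0.247 × 0.5 = 3.62%. The difference is 3.7 points, wider than 2.5.

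*Break-even.* Set the Case B difference equal to 2.5 and solve for r:
- q = 40%: 7.363 − 0.913 r = 2.5, so r = 5.3%
- q = 20%: 4.340 − 0.347 r = 2.5, so r = 5.3%

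Below about 5.3% the observed contrast is wider than the true one; above it, narrower.

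**The case against.** **The wording is loose.** The tests referred to include the OGTT, which Section 4.3 does not require. If the condition meant that any one of them was missing, the fallback would apply to almost everyone. But the condition would then have almost no work to do, and the plain reading is that none of the tests was done. The Insulin-treated diabetes subgroup does suggest that the authors meant treated patients to count. That supports correcting the sentence, not leaving it.

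**Sites will record treated diabetics as diabetic anyway.** They may, but classification would then depend on site habit. Section 6.2.1 leaves only its residual items to the clinical diagnosis in the record; diabetes has its own explicit rule.

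**The reach is narrow.** This stands. The study is exploratory and single-arm, and no hypothesis or error rate is attached to any subgroup. Three wider inferences are tempting but not supported:

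- *Bias toward no difference.* This needs controlled patients to carry about the same risk as other diabetics. The protocol does not say so, and Case B shows the contrast can widen.
- *A mismatch with RESET.* RESET's definition of diabetes is not given, and Section 8.1 names no covariates. Only the conditional statement holds: if diabetes is in the model, it carries this classification.
- *The same error in the report on non-enrolled patients (Section 4.2).* The tests are mandatory at enrollment. They are not mandated for patients who are not enrolled, so the fallback can apply there.

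**Conclusion.** The concern holds as a classification error in a rule the protocol itself states. Followed as written, the rule records enrolled patients with known, treated diabetes as non-diabetic when their values are below every threshold. The Diabetes subgroup is misdefined, and the rule conflicts with the Insulin-treated diabetes subgroup. The complementary Cox model is affected only if diabetes is a covariate.

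Confidence is high for the wording and low for the size. The 105–270 patients and the contamination of about 10–25% rest wholly on the assumed prevalence and share controlled. The contrast figures rest in addition on the assumed event rates. The direction of the effect is unknown.

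A reader might infer that the main conclusion is at risk. It is not: the exact binomial test against 6.6% uses the whole cohort and does not involve diabetes status. The point is worth correcting because the subgroup is pre-specified and the correction is very small.

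**What to change.** For data classification, replace the conditional second sentence in Section 6.2.1 by an or rule. Diabetes is present if any listed threshold is met, or there is a prior clinical diagnosis of diabetes, or the patient is currently on antidiabetic treatment, whether or not tests were performed. Use this one rule for the Diabetes and Insulin-treated diabetes subgroups and for any adjusted model that includes diabetes.

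The cost is one sentence and matching eCRF help text, with no added test or visit and no change to sample size, alpha or power. Concomitant medication at enrollment in Section 6.2.1 names only anticoagulation, so confirm that the eCRF records antidiabetic and insulin treatment, which the rule and the second subgroup both need.

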#### 4. Other items

Other items will be considered based on the clinical diagnosis described on the clinical record.

### 6.2.2 Follow-up at 12 months

At 12 months after enrollment, the following data will be recorded.

#### 1. Death

Investigation method to determine the patient's death/survival, date of the last confirmation of death/survival, presence/absence of death, date of death, classification of cause of death, cause of death

#### 2. Other events than death

Investigation method for other events than death, date of the last confirmation of other events than death, presence/absence of other events than death

#### 3. Myocardial infarction (MI)

Presence/absence of MI, date of onset, ST-elevation MI, Q-wave MI, relationship with stent thrombosis, ARC classification, presence/absence of evaluation of the maximum values of cardiac enzymes, date of measurement of cardiac enzymes, CK, CK-MB, troponin T, troponin I, lethality

#### 4. ACS

Presence/absence of emergency hospitalization due to ACS, date of onset, ACS classification, relationship with stent thrombosis, lethality

#### 5. Definite stent thrombosis according to ARC definition

Presence/absence of stent thrombosis, date of onset, situation of onset, presence/absence of evaluation of the maximum values of cardiac enzymes, date of testing, CK, CK-MB, troponin T, troponin I, presence/absence of Interim TVR trial, relationship with the surgical procedure, presence/absence of hemorrhagic complications before the onset of stent thrombosis, antiplatelet therapy (aspirin and thienopyridine drugs) at the onset of stent thrombosis, lethality

#### 6. Probable stent thrombosis according to ARC definition

Presence/absence of stent thrombosis, date of onset, classification (unexplained death within 30days / MI in the target vessel area)

#### 7. Possible stent thrombosis according to ARC definition

Presence/absence of stent thrombosis, date of onset

#### 8. Stroke

Presence/absence of stroke, date of onset, classification of stroke, lethality

#### 9. Heart failure

Presence/absence of hospitalization due to heart failure, date of onset

10. Ventricular fibrillation, persistent ventricular tachycardia

Presence/absence of hospitalization due to ventricular fibrillation or persistent ventricular tachycardia, date of onset

11. Hemorrhagic complications

Presence/absence of hemorrhagic complications, date of onset, site of hemorrhage, Nadir Hb, Nadir Ht, presence/absence of blood transfusion, presence/absence of drop in blood pressure, presence/absence of surgical hemostasis, TIMI classification, GUSTO classification, BARC classification

12. Surgery

Presence/absence of surgery, date of surgery, presence/absence of systemic anesthesia, surgical procedure, surgical area

13. CABG

Presence/absence of CABG, date of CABG

14. Other revascularizations than TLR

Presence/absence of other revascularizations than TLR, date of revascularization, method of revascularization, other TVRs than TLR, presence/absence of clinically indicated revascularization

15. TLR

Presence/absence of TLR, date of TLR, revascularization method, presence/absence of clinically indicated revascularization

16. Information about TLR lesion unit (to be recorded for each lesion)

Presence/absence of TLR, date of TLR, revascularization method, PCI device, presence/absence of clinically indicated revascularization, presence/absence of follow-up angiography, date of follow-up angiography, reason of follow-up angiography, evaluation method of follow-up angiography, presence/absence of restenosis in the main branch, presence/absence of reocclusion of the main branch, presence/absence of restenosis in collateral branches, presence/absence of reocclusion of collateral branches

17. Treatment discontinuation

Date of the last confirmation of thienopyridine treatment status, presence/absence of administration at the last confirmation date discontinuation of single drugs, date of discontinuation, reason of discontinuation, alternative drugs or measures taken, resumption of single drugs, date of resumption, discontinuation of thienopyridine treatments, date of discontinuation, reason of discontinuation, alternative drugs or measures taken, resumption of thienopyridine treatments, date of resumption, date of the last confirmation of aspirin treatment status, presence/absence of administration at the last confirmation date, discontinuation of aspirin treatment, date of discontinuation, reason of discontinuation, alternative drugs or measures taken, resumption of aspirin, date of resumption

### **6.2.3 Completion / Discontinuation of the Study**

If the study was completed or prematurely discontinued, date of the last contact with the subject, if the subject had completed the study, reason of discontinuation are recorded in the corresponding columns of

eCRF. In addition, if the study was prematurely discontinued reason of premature discontinuation is recorded.

## **7. ENDPOINTS**

### **7.1 Primary endpoint**

The primary endpoint in this study is a composite endpoint of cardiovascular death in 12 months, myocardial infarction (MI), stroke (ischemic and hemorrhagic), stent thrombosis (Definite stent thrombosis [ST] not resulting in MI) and serious bleeding (TIMI Major/Minor).

### **7.2 Secondary endpoints**

#### **7.2.1 Major secondary endpoints**

In this study, the following major secondary endpoints will be evaluated at 12 months after enrollment.

- Cardiovascular death/ MI/ stroke/ definite ST
- Major bleeding (TIMI Major/ Minor)

#### **7.2.2 Secondary Endpoints**

In this study, the following secondary endpoints will be evaluated at 12 months after enrollment.

- Death / MI
- Death
- Cardiovascular death/ MI
- Cardiovascular death
- MI
- Stroke
- ST (ARC definition)
- TLF
- TVF
- MACE
- Any TLR
- Clinically-driven TLR
- Non-TLR
- CABG
- Any TVR
- Any revascularization
- Bleeding complications

## **8. DETERMINATION OF SAMPLE SIZE**

### **8.1 Sample size required for safety assessment on the primary endpoint**

The primary endpoint in this clinical study is a composite endpoint of cardiovascular death, myocardial infarction (MI), stroke, stent thrombosis and serious bleeding at 12-month follow-up. The event rate for the primary endpoint in this single arm study will be compared against a Performance Goal (PG) of 6.6% using an exact test through the binominal distribution.

This PG of 6.6% is derived by adding a delta to the assumed true event rate. Based on the historical XIENCE V data in the RESET trial (4% with a sample size 1559; reference 7), the one-sided 80% confidence limit is approximately 4.4%. To account for variability associated with the observed rate of 4% in the RESET trial, the true rate in this proposed trial is assumed to be 4.4%. With a delta taken to be 2.2% (50% of the base rate of 4.4%), the final PG is 6.6% (4.4%+2.2%).

Given the following assumptions:

One-sided alpha 0.025

True rate 4.4% (event during hospitalization were excluded)

PG 6.6%

An exact test through binomial distribution is used to calculate the p-value

Power approximately 95%

An effective sample size of 1455 is required. Take into consideration of dropout cases, a total of approximately 1500 patients is needed.

In addition, for evaluating the primary endpoint, complementary analysis using Cox proportional hazard model also will be performed, to take into account the differences in patient background of the everolimus-eluting Stent (XIENCE™) group in RESET study.

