#### **4.2 Issued to be considered**

- Enrollment should be carried out after PCI with XIENCE Prime™ during the same hospitalization.
- The type and dose of aspirin are chosen according to the institute's guideline. The type and dose of thienopyridine should be equivalent to clopidogrel 75 mg/day. For patients who do not tolerate clopidogrel, this can be substituted with ticlopidine 200 mg/day.
- Administrations of antiplatelet drugs other than aspirin / thienopyridine are not acceptable.

- Patients can also be visited by the referring doctor, but Thienopyridine should be prescribed at the study institute.
- In discontinuing thienopyridine therapy, outpatient visit should be made in principle, and the discontinuation should be fully explained to the patient. F/U at 12 months after surgery should be performed at outpatient visit as far as possible. However, if the visit is impossible, F/U by telephone interview can be accepted. Incidence of any event should be recorded in the appropriate form.
- Although the planned follow-up period is 12 months, this can be prolonged if the Safety Evaluation Committee considers that safety must be followed up for a longer period.
- Acceptable time window for the discontinuation of thienopyridine therapy should be within  $\pm 1$  month.
- To ensure adherence to the administration schedule of thienopyridine, CRC of the study institute or equivalent staff communicates to the outpatient doctor the necessity of discontinuing the prescription of thienopyridine at the outpatient visit at 3 to 4 months after PCI, and confirms that the prescription of thienopyridine has been discontinued at the same visit.
- While initial enrollment is done by the investigator of each institute, data input, including PCI form, should be carried out by the institute's CRC or external CRC.
- Each institute should report the patients' background (age, sex, diagnosis, presence of diabetes mellitus, renal function, and target lesion) and the planned period of DAPT treatment even for the patients who receive XIENCE Prime™ implantation in the enrollment period and have not received any drug-eluting stents other than everolimus-eluting cobalt-chromium stent (XIENCE /PROMUS™) in the past, and who are not enrolled in this study.
- If planned staged PCI is scheduled, the patient will be enrolled after completion of all PCI. The last PCI should be the index procedure.

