### 11.2 Myocardial Infarction: MI

Myocardial Infarction (MI) is defined by the ARC criteria. However, periprocedural MI will be evaluated by CKMB, because the evaluation by troponin is too sensitive.

- **Baseline MI evaluation**  
EEG showing ST elevation, development of new abnormal Q-wave, clinical symptoms specific to MI, troponin or CK-MB values exceeding the standard values
- **Periprocedural MI**
  - Occurrence of any of the following events within 48 hours after PCI procedure will be judged as MI.
    - CK-MB  $\geq 3$  times Upper Reference Limit (URL) (CK-MB value exceeding URL before procedure is not considered as a new MI, but as MI at enrollment.)
    - Abnormal ECG (new Q-wave, left bundle branch block)
  - Occurrence of troponin  $\geq 5$  times URL or CK-MB  $\geq 5$  times URL within 72 hours after CABG procedure accompanied by any of the following criteria will be judged as

MI. (CK-MB value exceeding URL before procedure is not considered as a new MI, but as MI at enrollment.)

- Abnormal ECG (new Q-wave, left bundle branch block)
- New occlusion of coronary autografts or grafts
- Reduction in living myocardium confirmed by diagnostic imaging
- **Spontaneous MI**
  - Occurrence of any of the following events at > 48 hours after PCI or > 72 hours after CABG will be judged as MI. MI caused by revascularization procedures, such as TLR and TVR, is defined as periprocedural MI.
  - Abnormal ECG (new Q-wave, left bundle branch block)
  - Troponin or CK-MB value > **URL** (CK-MB value exceeding URL before procedure is not considered as a new MI, but as MI at enrollment.)
- **Sudden Death**
  - When death occurred before blood sampling for biomarker measurements or while biomarkers appeared to be increasing, MI will be judged according to the following criteria:
    - Clinical symptoms suggesting ischemia that are accompanied by one of the following:
      - New ST elevation or left bundle branch block
      - Thrombus determined by angiography or at autopsy
- **Reinfarction**
  - When after onset of MI stable or decreasing values are confirmed in 2 biomarker measurements, but 20% increase 3 to 6 hours is observed after the second measurement.
  - If biomarkers are increasing or have not yet reached the peak, data are insufficient to diagnose reinfarction.

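### The rate behind the 6.6% performance goal is stated to exclude in-hospital events, but the primary endpoint as worded does not carry that exclusion

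*Protocol*

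**What the plan says.** Section 8.1 sets the decision rule: the 12-month event rate is "compared against a Performance Goal (PG) of 6.6% using an exact test through the binominal distribution". The goal is built in a chain. It starts from RESET ("4% with a sample size 1559; reference 7"), then takes an upper bound ("the one-sided 80% confidence limit is approximately 4.4"%), then adds half of that bound. The list of assumptions repeats the middle figure with a condition: "True rate 4.4% (event during hospitalization were excluded". This is the only place in the protocol where in-hospital events are set aside.

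The endpoint compared with that goal is defined in 7.1 as a "composite endpoint of cardiovascular death in 12 months, myocardial infarction (MI), stroke (ischemic and hemorrhagic", together with definite stent thrombosis not resulting in MI and TIMI major or minor bleeding. Neither 7.1, the Summary nor the opening of 8.1 excludes in-hospital events or starts the count at discharge.

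The event definitions reach into the index stay. Section 11.2 says of periprocedural MI: "Occurrence of any of the following events within 48 hours after PCI procedure will be judged as MI". Section 11.4 includes acute stent thrombosis in the first 24 hours, and the TIMI criteria in 11.6 have no in-hospital exception. Under 4.2, enrollment follows PCI "during the same hospitalization".

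Time zero differs between sections. Section 6.1 places follow-up 12 months after the procedure. Section 6.2.2 says "At 12 months after enrollment, the following data will be recorded", and 7.2.1 and 7.2.2 also count from enrollment. Section 7.1 names no starting point.

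**The concern.** A single-arm comparison with a fixed goal is valid only if the observed rate and the goal count the same events. Here one side carries a stated exclusion and the other does not. An analyst who follows 7.1 and 11.2 to the letter would count a CK-MB rise on the day after the index PCI, or a bleed before discharge, and test the total against a threshold built without such events.

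Two things are at stake. First, in-hospital events occur well before thienopyridine is stopped at 3 months and say nothing about that decision, yet they could determine whether the goal is met. Second, the protocol leaves two defensible counts of the same data. As a hypothetical case, take 82 events among 1455 patients, 7 of them before discharge. The study fails on one count (82 exceeds the limit of 77) and succeeds on the other (75). In an open, single-arm study, that choice should not be available once the events are known.

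**Working it through.** **Inputs, all from section 8.1:** RESET rate 4% with n = 1559; base rate 4.4%; delta 2.2%; goal 6.6%; one-sided alpha 0.025; exact binomial test; effective n = 1455; power about 95%; total 1500.

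**Step 1: reproduce the goal.** One-sided 80% upper limit by the normal approximation: 0.04 + 0.8416 × √(0.04 × 0.96 / 1559) = 0.04 + 0.0042 = 4.42%. The exact (Clopper-Pearson) limit with 62 of 1559 is 4.45%. Either agrees with about 4.4%. Then 4.4% + 0.5 × 4.4% = 6.6%. Because 4.4% is only the upper limit of the 4%, and 6.6% is 1.5 × 4.4%, a condition attached to the 4.4% has to hold along the whole chain for the chain to be coherent.

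**Step 2: reproduce the sample size.** Take the largest c with P(X ≤ c | 1455, 0.066) ≤ 0.025. This gives c = 77 (5.29%), with attained alpha 0.0225. Power = P(X ≤ 77 | 1455, 0.044) = 95.4%. Dropout: 1455 / 0.97 = 1500. The stated design reproduces, so the problem is not arithmetic.

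**Step 3: count in-hospital events but leave the goal at 6.6%.** Let h be the percentage points that in-hospital events add. The protocol gives no value, so h is an assumption. Power = P(X ≤ 77 | 1455, 0.044 + h).

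| Assumed h (points) | Counted rate | Expected events (1455 × rate) | Power |
|---|---|---|---|
| 0 | 4.40% | 64.0 | 95.4% |
| 0.25 | 4.65% | 67.7 | 88.8% |
| 0.5 | 4.90% | 71.3 | 77.7% |
| 1.0 | 5.40% | 78.6 | 45.7% |
| 2.0 | 6.40% | 93.1 | 4.4% |

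The design has room for 77 − 64 = 13 events above expectation, which is 13 / 1455 = 0.9 points. Small additions therefore matter. The last row uses nearly all of the 2.2-point delta and is shown only as the end of the range.

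**Step 4: direction.** At a counted rate of exactly 6.6%, the chance of success is 2.25%. A strategy whose post-discharge rate is 6.6% has a higher counted rate once in-hospital events are added, so its chance of success is lower still. At a counted rate of 7.4%, for example, it is 0.08%. The mismatch cannot help an unsafe strategy pass.

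**Step 5: put both sides on one basis.**

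- Exclude in-hospital events from the study endpoint as well: h = 0, so 6.6%, 1455 and 95.4% are unchanged.
- Include them in both, with the goal rebuilt as 1.5 × (4.4% + h): the goal is 7.35% at h = 0.5 and 8.1% at h = 1.0, with power of 97.3% and 98.4% at n = 1455. Part of this gain arises because the delta is proportional and widens in absolute terms (2.7 points at h = 1.0).

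The loss in step 3 comes from the mismatch alone.

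**The case against.** The strongest reply is that 7.1 is silent rather than inclusive. The only explicit statement on in-hospital events is in 8.1, where it is attached to the true rate assumed for this trial. The natural inference is that the authors meant to leave them out here. The Summary and section 3 also say that the goal comes from the incidence of the same primary endpoint in RESET, so like was meant to be compared with like. This largely stands as an account of intent. A reader might infer that the study deliberately tests one endpoint against a goal for another; the documents do not support that. They show an exclusion stated once and not carried into the definition that governs the count.

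Other parts of the reply also hold:

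- The 48-hour rule in 11.2 also serves later procedures, since MI caused by TLR or TVR is classed as periprocedural. Its presence does not prove that index-procedure MI enters the primary endpoint. It does mean that nothing in 11.2 keeps it out.
- Events between PCI and enrollment count only if the clock starts at the procedure, and the physician's judgement before enrollment may remove some patients with early complications. Events between enrollment and discharge fall inside the window on either clock.
- A reader might see three clocks. In this text, surgery and procedure both mean the index PCI, so there are two.
- A reader might infer that the complementary Cox comparison with RESET is also mismatched. Section 8.1 states no event window for that model, so this is a risk to close and not an error to assert.

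The analysis plan, which is not at hand, may give a counting window. The conflict nevertheless lies within the protocol, between the endpoint it defines and the goal it fixes.

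**Conclusion.** The concern holds as an inconsistency in the primary decision rule. The rate from which 6.6% is built is stated to exclude in-hospital events, and the endpoint as worded does not apply that exclusion. Followed literally, the observed rate and the goal count different events.

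The consequence runs in one direction. It raises the chance of false failure, from about 5% to about 11%, 22% or 54% for assumed additions of 0.25, 0.5 or 1.0 points, if the post-discharge rate is 4.4%. It does not inflate type I error, and a reading that an unsafe strategy could pass because of it would be wrong. The remaining harm is that the event count depends on a choice the protocol leaves open.

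The size rests wholly on the assumed in-hospital rate. That the exclusion also applied to the RESET 4% is inferred from the chain in 8.1 and should be confirmed by the sponsor.

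**What to change.** 1. In 7.1, and wherever the primary endpoint is restated, say that it counts events after discharge from the index hospitalization up to 12 months after the procedure. Report in-hospital events, including index-procedure MI, separately. State how patients who die before discharge are handled in the denominator.
2. In 11.2, note that periprocedural MI from the index PCI is not counted in the primary endpoint, while MI from later procedures is.
3. Use one time zero in 4.2, 6.1, 6.2.2 and 7.
4. Confirm that the RESET 4% was counted on the same window, and apply that window to the RESET patients in the Cox comparison.

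With these changes 6.6%, 1455 and about 95% power stand. If in-hospital events are meant to count, rederive 4%, 4.4% and 6.6% from RESET with them included, and justify the wider absolute delta that results.

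The cost is protocol wording plus one data item. The items listed in 6.2.1 to 6.2.3 include the date of hospitalization and event onset dates but no discharge date, so that field must be added or retrieved from the sites. The change should be made before event data are reviewed.
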